## Abstract

**Introduction:** Small intestinal bacterial overgrowth (SIBO) leads to non-specific abdominal discomfort and nutrient malabsorption. Currently, rifaximin is widely applied in SIBO based on its antibacterial and non-absorbable nature. Berberine is a natural component of many popular medicine plants that ameliorates intestinal inflammation in humans through its modification of the gut microbiota. Potential effect of berberine to the gut may provide therapeutic target for SIBO. We aimed to evaluate the effect of berberine compared with rifaximin on SIBO patients.

**Methods:** This is an investigator-initiated, single-center, open-label, double-arm randomized controlled trial, termed BRIEF-SIBO (Berberine and rifaximin effects for small intestinal bacterial overgrowth). In total, 180 patients will be recruited and allocated to an intervention group (berberine) and a control group (rifaximin). Each participant will receive one 400 mg drug twice a day (800 mg daily) for 2 weeks. The total follow-up period is 6 weeks from the start of medication. The primary outcome is a negative breath test. The secondary outcomes include abdominal symptom relief and alteration in gut microbiota. Efficacy assessment will be performed every 2 weeks, as well as safety assessment during the treatment. The primary hypothesis is that berberine is not inferior to rifaximin for SIBO.

**Discussion:** The BRIEF-SIBO study is the first clinical trial assessing the eradication effects of 2 weeks of berberine treatment in SIBO patients. The effect of berberine will be fully verified by using rifaximin as the positive control. The findings of this study may have implications for the management of SIBO, especially increasing the awareness of both physicians and patients who are suffering from long-term abdominal discomfort and avoiding excessive examination.

## 1 Introduction

Small intestinal bacterial overgrowth (SIBO) is defined as the presence of an abnormally excessive amount of bacterial colonization in the small bowel (Quigley et al., 2020; Bushyhead and Quigley, 2022). Primary or secondary motility abnormalities destroy the ability of the small intestine to prevent colon bacterial translocation (Bohm et al., 2013). Meanwhile, ileocecal valve dysfunction leads to colonic bacterial regurgitation (Miller et al., 2012). It is believed that symptoms linked to SIBO consist of bloating, diarrhea and abdominal pain/discomfort. Steatorrhea, vitamin B_12_ deficiency and malnutrition can be seen in more severe cases.

The gold standard for the diagnosis of SIBO is quantitative culture of small intestine aspirates. The American Gastroenterology Association (AGA) recently recommended a new threshold at >10^3^ colony-forming units per milliliter (CFU/mL) on fresh aspirate culture instead of >10^5^ CFU/mL based on a large-scale study (Leite et al., 2019), derived from subjects with altered intestinal anatomy because the bacterial level in normal subjects rarely exceeds 10^2^ CFU/mL (Pimentel et al., 2020). An alternative method is the measurement of exhaled hydrogen and methane gas, which is considered a non-invasive, safe, useful, and cost-efficient test (Hammer et al., 2022). The North American Consensus recommended that a rise in hydrogen of ≥20 part per million (ppm) or methane levels ≥10 ppm by 90 min during glucose or lactulose breath test was considered positive (Rezaie et al., 2017).

SIBO is now commonly diagnosed and closely associated with many gastrointestinal diseases, such as irritable bowel syndrome (IBS) (Ghoshal et al., 2020), inflammatory bowel disease (IBD) (Shah et al., 2019), pancreatitis (El Kurdi et al., 2019), non-alcoholic liver disease (Wijarnpreecha et al., 2020), colorectal cancer and abdominal surgery. Based on the similarity of the clinical manifestation profiles between IBS and SIBO, the prevalence of SIBO in IBS patients has been widely reported to range from 4% to 84%, with an overall pooled prevalence rate of 38% (Chen et al., 2018). A meta-analysis of case‒control studies found that SIBO prevalence in patients with IBS was 35.5% (95% CI 33.6–37.4) and 29.7% (95% CI 27.6–31.8) in controls based on breath tests, while culture-based studies yielded a SIBO prevalence of 33.5% (95% CI 30.1–36.9) in patients with IBS and 8.2% (95% CI 6.8–9.6) in controls with a cutoff value of 10^3^ CFU/mL (Shah et al., 2020). The diagnostic modality actually influences the prevalence of SIBO in consideration of the sensitivity and specificity of breath tests.

Currently, rifaximin is widely applied considering its broad-spectrum and non-absorbed nature to achieve low gastrointestinal absorption while retaining good antibacterial activity, which is thought to be effective and safe for the treatment of SIBO (Gatta and Scarpignato, 2017). Studies have shown significant symptom remission of rifaximin therapy in IBS patients with SIBO (Moraru et al., 2014; Liu et al., 2016; Leite et al., 2018; Rezaie et al., 2019; Tuteja et al., 2019). Unfortunately, no responsiveness and recurrence after eradication of SIBO limit antibiotic usage. Rezaie et al. (2019) reported that 48/93 (51.6%) were non-responders after 2 weeks of low-dose rifaximin treatment. For those responders, the average time of recurrence was 94.86 ± 38.6 days, and 38 (84.4%) of the 45 patients experienced symptom recurrence by the end of the 18-week observation phase. Moreover, we must take into account that rotating antibiotic regimens lead to drug resistance and risks of *Clostridium difficile* infection. Medication for SIBO remains confusing and limited.

Berberine is a natural pentacyclic isoquinoline alkaloid extracted from many popular medicine plants such as the genus *Berberis*, *Coptis* and *Hydrastis* (Wang et al., 2017). There is already evidence that the structural and numerical changes in the gut microbiota under pathological conditions can be reversed by berberine (Jia et al., 2019), which mediates modulatory effects on microglial activation and visceral hypersensitivity (Zhang et al., 2021), and ameliorates intestinal inflammation in humans through antibacterial action (Gong et al., 2017; Habtemariam, 2020). Berberine enhanced the composition of beneficial bacteria such as *Bacteroides*, *Bifidobacterium*, *Lactobacillus*, and *Akkermansia* (Fang et al., 2021). Furthermore, it could alleviate colon inflammation by regulating interferon-gamma and interleukin-17A-producing lamina propria CD4 (+) T cells (Takahara et al., 2019). It has been proven to significantly decrease diarrhea and abdominal pain scores in diarrhea-predominant IBS patients (Chen et al., 2015). Berberine effects to the gut may provide therapeutic targets for SIBO. Chedid et al. (2014) confirmed that herbal therapy containing berberine is equivalent to rifaximin for the resolution of SIBO. However, there is little evidence investigating the potential effect of berberine as a single agent in SIBO patients. In the present study, we aimed to evaluate the effects of berberine and rifaximin on patients with SIBO (BRIEF-SIBO study). The effectiveness outcomes included a negative lactulose hydrogen methane breath test (LHMBT) and clinical symptom remission. Different gut microbiome spectra in SIBO patients treated with berberine and rifaximin may provide a potential explanation.

## 2 Methods and analysis

### 2.1 Trial design

This is an investigator-initiated, single-center, open-label, two-arm randomized controlled trial from Peking University Third Hospital, Beijing, China, termed BRIEF-SIBO. The study aims to evaluate the efficacy and safety of berberine for SIBO patients compared with rifaximin as the positive control. This study was registered on the Chinese Clinical Trial Registry platform under number ChiCTR2200057554. The study protocol, informed consent and other documents were reviewed and approved by the Peking University Third Hospital Medical Science Research Ethics Committee under number 2022-021-02. This protocol complies with the Standard Protocol Items: Recommendations for Interventional Trials (SPIRIT) (Chan et al., 2013).

### 2.2 Patient recruitment and eligibility

Patients who have at least one of the major symptoms, including abdominal pain, distension, diarrhea or constipation, with positive LHMBT will be enrolled in this study. The inclusion criteria were as follows: 1) Aged ≥18 and ≤65 years old; 2) Complained of abdominal pain, distension, constipation or diarrhea for over 6 months, and at least one of them up to a moderate or severe degree according to the gastrointestinal symptom rating scale (GSRS); 3) Positive hydrogen breath test with elevated or normal methane gas; 4) Voluntarily joined the study and completed the case report form, LHMBT, colonoscopy and blood biochemical examination; and 5) Took drugs according to the required rules with good compliance.

Patients who were found to have gastrointestinal organic diseases detected by endoscopy or digestive tract surgery history were excluded. Patients with severe heart, liver, lung, kidney, blood, endocrine, and nervous system diseases, or severe respiratory tract, digestive tract, urinary tract infections or mental disorders will temporarily stop entering treatment until professional clinicians access their conditions. Patients who were taking antibiotics and acid suppression drugs for more than 3 days during the past month or probiotics, laxatives, antidiarrheal or prokinetic agents within 2 weeks will not be eligible for participation. Pregnant or lactating women will also be excluded. Patients who firmly report rifaximin or rifamycin allergy will not participate, as it is possible to be randomized to the rifaximin group. All patients will be identified through gastroenterologists for their patients with non-specific abdominal symptoms. Two principal researchers of the project team are responsible for explaining the background, purpose, process, risks and benefits of this study and obtaining informed consent.

### 2.3 Visit and procedure

#### 2.3.1 Screening

The study flow diagram is shown in Figure 1 (Schulz et al., 2010). We will first perform LHMBT for those suspected to have SIBO and exclude negative patients. The next examination is colonoscopy to ensure that they do not have organic colon diseases. Baseline measures include a case report form (shown in Supplementary Material), regular blood tests, stool collection for calprotein and 16S rRNA sequencing. Blood samples will be collected and shipped to the core laboratory. Stool samples will be stored at −80°C.

**FIGURE 1 F1:**
[figure not shown]
Flow diagram based on the Consolidated Standards of Reporting Trials guidelines (CONSORT): Neg, negative; CRF, case report form.

Before LHMBT, all subjects are supposed to refrain from antibiotic use and discontinue probiotics, laxatives, antidiarrheal and prokinetic agents for 2 weeks. To minimize basal hydrogen excretion, dietary restriction and avoidance of smoking for at least 24 h prior to the test and during the test are recommended. Furthermore, patients are required to avoid coarse grains, milk, juice, and alcohol in the evening before the test. Fasting for 8–12 h before the procedure is needed. Before the examination, subjects use 20 mL antiseptic mouthwash (0.05% chlorhexidine) to eliminate fermentation by oral bacteria. End-expiratory breath samples will be collected just before the ingestion of 10 g (15 mL) of lactulose in a 250 mL water solution. Gas samples are collected every 15 min until 90 min and tested immediately by the methane-hydrogen breathing analyzer DA6000 (Sunvou Medical Electronics Co., Ltd., Wuxi, China). A rise in hydrogen of ≥20 part per million (ppm) by 90 min with elevated or normal methane was considered positive. Patients with only methane levels ≥10 ppm are not eligible (Rezaie et al., 2017).

#### 2.3.2 Intervention

In total, 180 patients will be recruited and divided into two groups: the berberine group (Berberine Hydrochloride Tablets, H51022193, Chengdu Jinhua Pharmaceutical Co., Ltd., China) and the rifaximin group (Xifaxan, H20181212, Alfasigma S.p.A, Italy). Each participant will receive only one 400 mg drug twice a day (800 mg daily) for 2 weeks. The recommended dose of berberine is mainly determined by the advice of pharmacological experts, while that of rifaximin is based on past clinical trial conclusions. The first participant was enrolled on 15 March, 2022, and the study is expected to be terminated by July 2023 with the anticipated inclusion of 180 participants.

#### 2.3.3 Follow-up

The total follow-up period is 6 weeks from the start of medication. Efficacy assessment will be performed every 2 weeks using GSRS (Dimenäs et al., 1993), Bristol Stool Form (BSF) and breath tests, as well as safety assessment during the first 2 weeks of treatment. Each specific visit and measurement are summarized in Table 1. Multiple methods, such as telephone and online follow-up, are carried out to improve patient compliance if room consultation is impossible. Participants will return unused tablets and report reasons for non-compliance at the first visit (Kini and Ho, 2018). If a patient decides to withdraw, the follow-up will be stopped.

**TABLE 1 T1:** Standard protocol items: Adapted recommendations for interventional trials (SPIRIT) schedule: Enrollment, interventions, and follow-up.

	Screening	1 week	2 weeks	4 weeks	6 weeks
Case report form	×				
GSRS and BSF	×		×	×	×
Breath test	×		×	×	×
Blood test	×				
Enteroscopy	×				
Stool 16S rRNA sequencing	×		×	×	×
Medication record		×	×		
Adverse event		×	×		

Legend: GSRS, gastrointestinal symptom rating scale; BSF, bristol stool form.

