#### 2.4.2 Assessment of harms

The study investigator will exclude those with any physical problems that may limit participation with berberine or rifaximin exposures. Participants will be asked to report any adverse events (AEs) experienced during the study period. Participants with adverse events (e.g., dizziness, headache, loss of taste, dull sensation, diplopia, vertigo, palpitations, hot flashes, dyspnea, hematochezia, rash, back pain, muscle spasm, muscle weakness, hematuria, fever, flu-like symptoms after intervention) will be advised to consult their physician to provide healthcare as appropriate. The investigator will record the details of the frequency and severity of adverse events.

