### 2.9 Statistical analysis

Patients who finish at least one postmedication evaluation after randomization and subsequent treatment constitute the study full analysis set (FAS) as well as the primary group of efficacy assessment, according to the intention to treatment (ITT) principle. Patients who meet the criteria and complete the observation before medication without other affected treatments during the trial will be included in the study per protocol set (PPS) as the secondary group of efficacy assessment. The study safety set consists of all cases who have safety evaluation data after taking at least one kind of drug. Rubin’s method of multiple imputation will be performed for missing values to restore natural variability and uncertainty. The complete and imputed datasets will be combined and analyzed (Little et al., 2012). Complete case analysis is used for fecal microbiota on the nature of the outcome.

Analysis will be conducted using SPSS V.26.0. The quantitative and qualitative variables were reported as mean ± standard deviation (SD), median ± interquartile range (IQR), and number (frequency). Univariate analysis of variance (ANOVA) will examine differences between groups for variables with continuous data. χ2 tests will examine differences between groups for categorical variables. Unadjusted ANOVA and adjusted analysis of covariance models will compare differences in scores from baseline and postintervention data within and between groups using FAS and PPS. Variable correlations will be analyzed through Spearman’s correlation analysis. Statistical significance was defined as a *p*-value less than 0.05.

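### The protocol gives two adverse event windows: the schedule stops at week 2, while the harms section covers the study period, and follow-up runs to week 6

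*Protocol article*

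**What the plan says.** Treatment is short and follow-up is longer. On treatment, Section 2.3.2 states: "Each participant will receive only one 400 mg drug twice a day (800 mg daily) for 2 weeks". On follow-up, Section 2.3.3 states: "The total follow-up period is 6 weeks from the start of medication".

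Three places tie safety assessment to the treatment phase:

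- the abstract: "Efficacy assessment will be performed every 2 weeks, as well as safety assessment during the treatment";
- Section 2.3.3: "as well as safety assessment during the first 2 weeks of treatment";
- Table 1, where the adverse event row is marked at 1 and 2 weeks and is blank at 4 and 6 weeks.

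Table 1 is not a loose illustration. Section 2.3.3 gives it the role of the full schedule: "Each specific visit and measurement are summarized in Table 1".

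Section 2.4.2, on harms, uses a wider term: "Participants will be asked to report any adverse events (AEs) experienced during the study period". It adds that the investigator records how often events occur and how severe they are.

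Section 2.9 defines the safety population without naming a time window: "The study safety set consists of all cases who have safety evaluation data after taking at least one kind of drug".

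**The concern.** Someone working from Table 1 would carry out no adverse event assessment at weeks 4 and 6, although the same table has patients giving a breath test, symptom and stool-form scores and a stool sample at both. Someone working from Section 2.4.2 would expect events to be gathered throughout the study. Both readings rest on current text, and they lead to different data.

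Two things are at stake. The first is the meaning of the reported rate. A proportion of patients with an adverse event over 2 weeks is not the same quantity as one over 6 weeks, and the article does not say which will be given. The second is how later events reach the record. If they are not asked about on a schedule, they are recorded when a patient happens to raise them. Patients know their treatment (Section 2.5), so the tendency to raise an event could differ by arm. This matters because Section 2.1 names safety against rifaximin as part of the trial's aim.

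**Working it through.** The article states no adverse event rate or other figure to reproduce here. The check sets the passages side by side and then does one subtraction.

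**Step 1. Inputs.**

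| Item | Value | Source |
|---|---|---|
| Treatment duration | 2 weeks | Section 2.3.2 |
| Follow-up from start of medication | 6 weeks | Section 2.3.3 |
| Post-baseline time points | 1, 2, 4 and 6 weeks | Table 1 |
| Adverse event marks | 1 and 2 weeks | Table 1 |
| Symptom and stool-form scores, breath test, stool sequencing (post-baseline marks) | 2, 4 and 6 weeks | Table 1 |
| Safety assessment in the text | treatment phase | Abstract; Section 2.3.3 |
| Adverse event reporting in the text | study period | Section 2.4.2 |

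**Step 2. Could the blank cells be a fault of text extraction?** This is unlikely. The abstract and Section 2.3.3 state the same limit in words, so the restriction does not depend on how the table was read.

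**Step 3. Does any other section settle the window?** No. The safety set in Section 2.9 sets none. Section 2.8 has the monitor include adverse events in a report on each participant, but does not say up to which week. Section 2.7 deals with reporting severe or unanticipated events and also gives no window.

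**Step 4. Size of the gap under Table 1.**

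- Follow-up with scheduled assessment: 2 / 6 = 33%.
- Follow-up without it: 6 − 2 = 4 weeks; 4 / 6 = 67%.
- Time points with assessment: 2 of 4.

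**Step 5. Under the wider wording.** If Section 2.4.2 governs and the study period is the 6-week follow-up, scheduled assessment would cover 6 of 6 weeks and 4 of 4 time points. The two added time points already exist for other measurements.

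**The case against.** The strongest reply is that the passages can be read together: scheduled assessment during dosing, plus patient reporting throughout. Section 2.4.2 does say that participants will be asked, and the monitoring and serious-event texts carry no week-2 limit. A reader might infer from Table 1 that events after week 2 are simply never asked about. The documents do not support that. What stands is narrower: no assessment is *scheduled* at weeks 4 and 6, and the harms section does not say when or how its wider request is carried out.

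Four further inferences are tempting and should not be made.

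- **That 67% of events are lost.** The 67% is calendar time. Scheduled assessment covers the whole dosing phase (2 of 2 weeks), and the article gives no figure for how many events would arise later.
- **That the safety comparison will look cleaner than it is.** This presumes a number and direction of late events that nothing in the article supplies. The window is the same in both arms. Differential reporting is possible in an open-label trial but is not shown.
- **That *Clostridium difficile* infection makes the late window critical.** The Introduction says that "rotating antibiotic regimens lead to drug resistance and risks of" this infection. It speaks of rotating regimens rather than one 2-week course, and says nothing about when the infection appears.
- **That Section 2.7 brings new treatments into weeks 3 to 6.** It offers alternatives for limited symptom response but gives no timing.

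It is also fair to say that an on-treatment window can be a legitimate choice for a 2-week course, that safety is not listed as a primary or secondary outcome, and that a condensed article may leave the layout of safety tables to a fuller document. None of this removes the conflict, because the article itself states both windows. The symptom and stool-form scores at weeks 4 and 6 do not fill the gap either, since Section 2.3.3 assigns them to efficacy.

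**Conclusion.** The point holds as an inconsistency in the adverse event window. The abstract, Section 2.3.3 and Table 1 schedule safety assessment during treatment only. Section 2.4.2 promises reporting over the study period. Nothing else in the article decides between them. Following Table 1, the last 4 of 6 weeks have no scheduled assessment, and the period to which an adverse event rate refers is undefined.

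This rests on one assumption: that the study period means the 6-week follow-up. The article does not define the term, so the equation is plausible but inferred. If the term was meant to cover dosing only, the gap disappears as a conflict, but Section 2.4.2 would still need rewording.

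The consequence is limited to the safety data. The primary outcome, the sample size and the non-inferiority conclusion are untouched. The change is worth making because it is cheap and safety is a stated aim.

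**What to change.** Reconcile the passages so that one window applies throughout:

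1. In Table 1, mark the adverse event row at the existing 4-week and 6-week time points.
2. Reword Section 2.3.3 and the abstract so that safety assessment runs to week 6, in line with Section 2.4.2, and state in Section 2.4.2 that the study period is the 6-week follow-up.
3. Ask the same adverse event questions in both arms at every time point, so that later events do not depend on who volunteers them.
4. In the safety set already defined in Section 2.9, report events on treatment (weeks 0–2) and after treatment (weeks 3–6) separately. This keeps the 2-week comparison intact and makes the period behind each rate explicit.

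If only the treatment phase was intended, Section 2.4.2 should say so and reported rates should be labelled as 2-week rates. That would remove the contradiction but leave the later weeks without scheduled safety data.

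The cost is a few minutes at two existing contacts (Section 2.3.3 already allows telephone or online follow-up), two table marks and small text edits. No dose, treatment or clinical rule changes. Recruitment had begun when the article was written, so patients already past week 6 would lack the added assessments; the report should say from which date the change applied.
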